### Definitions

In this trial, exclusive breastfeeding means that the infant exclusively receives breast milk after discharge from the hospital, regardless of feeding mode. In Denmark, and hence in this trial, exclusive breastfeeding allows for supplementing with, e.g., water and/or a maximum of one meal of infant formula per week [7]. Partial breastfeeding means that, in addition to breast milk, the baby receives infant formula or other diet elements several times a week or daily.

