#### Primary outcome measure

Proportion of mothers who exclusively breastfeed at four months postpartum.

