### Sample size and power calculations

For sample size calculation, an estimated eight clusters in each arm were used, totalling 16 clusters. Expected participation rate was 80% with 30% attrition from the first questionnaire at one week postpartum to the third questionnaire at four months postpartum. A power calculation was made using breastfeeding frequencies from 2016 made available from The National Child Health Register [50]. The ambition was to raise the proportion of women breastfeeding at four months in the intervention clusters to the national level. In the design phase, we obtained data on the mean prevalence of breastfeeding at four months in the project regions (49%) and at national levels (56%) in 2016 from the National Child Health Register. The observed difference in the proportion of women exclusively breastfeeding for a minimum of four months corresponds to an odds ratio of 1.32. In the power calculations, an interclass correlation coefficient (ICC) of 0.001, as observed in the previous intervention study [27], was used. Reaching a statistical power of 80% with a 5% significance level is thus achievable provided data are collected from 111 mothers in each cluster. In each cluster, the sample size was extended to ensure that a minimum of 52 mothers were young or had low educational attainment. This yields a power of 80% to investigate an increase in exclusive breastfeeding at four months from 45 to 55% in this subgroup.

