**Primary**							
Exclusive breastfeeding four months (binary)			X				*NCHR*
Exclusive breastfeeding (continuous)	X	X	X				*NCHR*

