### Statistical methods

We use random allocation to remove any influence of both measured and unmeasured variables on treatment allocation. Before conducting regression analyses, descriptive statistics will be applied to assess selection into the trial, baseline equivalence of trial arms and loss to follow-up.

Regression analyses will be applied when analysing primary outcomes. We will account for the clustered nature of data by using random effects models for binary and continuous outcomes [51] and shared frailty models for analysing time-to-event and recurrent events in continuous outcomes [52]. Intention-to-treat analyses will be conducted. These analyses will include all mother-infant dyads in the relevant trial arms irrespective of their compliance or loss to follow-up. Complete-case analyses will be conducted restricted to observations with available outcome measures [53]. For the intention-to-treat analyses, the survey data will be linked to the Danish national registers including all births; and missing outcome data will be handled by inverse probability weighting and missing covariates by multiple imputation from the registers. The probability weights will be estimated by conducting logistic regressions with outcome data (yes vs. no) as dependent variable and the following baseline variables as predictors: maternal educational, maternal age, cohabitation status, partner’s education, household income, occupational status, maternal smoking status, maternal BMI, and maternal as well as paternal psychiatric histories.

The effect of the intensified intervention will be examined by including an interaction term between treatment arms and a binary indicator of the mother being young or having low educational attainment.

All models will be analysed with treatment alone and adjusted for known predictors for breastfeeding duration collected in the survey (smoking status, maternal age, maternal education, parity, mode of delivery, maternal BMI and cohabitation status) and for design variables used in the randomisation (region of Denmark and number of annual births (< 900 births/year vs. ≥ 900 births/year). As the randomisation will hopefully have distributed the characteristics evenly between trial arms, these adjustments are made to increase the robustness of the effect estimations. Missing predictors will be imputed using multiple imputations and the results compared to the complete case analysis.

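### Feeding status reported at one week and one month is not used in the binary primary analysis, so the four-month proportion is overstated if early stoppers respond less than their baseline variables predict

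*Protocol article*

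**What the plan says.** The primary outcome is given under Primary outcome measure as "Proportion of mothers who exclusively breastfeed at four months postpartum". In Table 3, the row that begins "Exclusive breastfeeding four months (binary" is marked in the survey at four months only, with the National Child Health Register as register source. The row that begins "Exclusive breastfeeding (continuous" is marked at one week, one month and four months. The trial therefore holds early reports of feeding status.

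Under Definitions, "exclusive breastfeeding means that the infant exclusively receives breast milk after discharge from the hospital". The sample size section describes the planning difference as one in "women exclusively breastfeeding for a minimum of four months".

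Under Statistical methods, the complete-case rule is "Complete-case analyses will be conducted restricted to observations with available outcome measures". Of the intention-to-treat analyses it says "These analyses will include all mother-infant dyads in the relevant trial arms irrespective of their compliance or loss to follow-up". Missing outcomes there are handled by inverse probability weighting, and the weights come from "logistic regressions with outcome data (yes vs. no) as dependent variable". The listed predictors are all baseline variables: education, age, cohabitation, partner's education, income, occupation, smoking, BMI and parental psychiatric history. Neither feeding status at one week or one month nor trial arm is on the list.

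The sample size section counts attrition from the first to the third questionnaire. Recruitment to the survey stops on the number of mothers with data from the first three questionnaires. Both fit a reading in which the outcome is available when the four-month questionnaire has been answered.

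**The concern.** A mother who reports at one month that she has stopped breastfeeding has told the trial almost everything it needs for the four-month outcome. If she then skips the four-month questionnaire, the complete-case analysis as written leaves her out. The weighted analysis replaces her with responders of similar baseline profile, many of them still breastfeeding. Weighting on baseline variables cannot correct for a dropout process that depends on what happened after baseline.

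It is plausible that mothers who have stopped are less willing to keep answering a breastfeeding survey. The link could also differ by arm. Allocation is not concealed, and under Intensified intervention, telephone follow-up ends when a mother on it ceases breastfeeding, which can happen in one arm only. The survey is sent separately, so an effect on response is possible but not shown. At stake are the level of the four-month proportion (which also feeds the cost-effectiveness analysis) and, under narrower conditions, the arm difference.

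**Working it through.** **The plan's own figure.** Inputs from Sample size and power calculations: 49% v 56%, 8 clusters per arm, ICC 0.001, 5% significance (taken as two-sided), 80% power.
- Individually randomised n per arm = [1.960·√(2·0.525·0.475) + 0.842·√(0.49·0.51 + 0.56·0.44)]² / 0.07² = 798.
- Solving m = 798·(1 + (m − 1)·0.001)/8 gives m = 110.7, which is the stated 111.
- The odds ratio is (0.56/0.44)/(0.49/0.51) = 1.32, as stated.

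The sample size is correct and this point does not touch it.

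**Overstatement.** From the plan: true proportions p of 49% and 56%, overall dropout d = 30%. Assumed, because the documents give no figure: the share s known to have stopped by one month (10–30% control, 9–27% intervention), and the ratio r of dropout in stoppers to dropout in others. It is also assumed that stoppers are all 'no' at four months and that baseline variables explain none of the link.
- Dropout among non-stoppers: dc = d/(s·r + 1 − s).
- Complete-case proportion: p·(1 − dc)/(1 − d).

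For s = 20%, r = 2, control: dc = 0.30/1.20 = 0.25, and 0.49·0.75/0.70 = 52.5%.

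| s, control / intervention | r | Control (true 49%) | Intervention (true 56%) | Difference, points |
|---|---|---|---|---|
| any | 1 | 49.0% | 56.0% | 7.0 |
| 10% / 9% | 1.5 | 50.0% | 57.0% | 7.0 |
| 10% / 9% | 2 | 50.9% | 58.0% | 7.1 |
| 20% / 18% | 1.5 | 50.9% | 58.0% | 7.1 |
| 20% / 18% | 2 | 52.5% | 59.7% | 7.2 |
| 30% / 27% | 1.5 | 51.7% | 58.9% | 7.1 |
| 30% / 27% | 2 | 53.8% | 61.1% | 7.3 |

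If the baseline variables do not predict the link, the planned weights are flat and the weighted analysis returns the same figures. If they explain part of it, the excess is smaller.

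**Arm difference** (s = 20% / 18%, true difference 7.0; differences taken before rounding).
- Dropout 30% in both arms, r = 2 in the intervention arm only: 59.7% − 49.0% = 10.7 points.
- The same with r = 2 in control only: 56.0% − 52.5% = 3.5 points.
- r = 2 in both arms, dropout 25% control and 35% intervention: 60.6% − 51.7% = 8.9 points. With the dropout rates reversed: 58.8% − 53.4% = 5.5 points.
- r = 1 in both arms, dropout 25% v 35% either way: 7.0 points, unbiased.

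**Check of the remedy** (control, s = 20%, r = 2).
- Non-stoppers who respond: 0.80·0.75 = 0.60, of whom 0.49·0.75 = 0.3675 are 'yes'.
- Weighting them by 1/0.75 gives 0.49 'yes' out of 0.80. Adding stoppers at weight 1 gives 0.49/(0.80 + 0.20) = 49.0%, the true value.
- The same coding without weights gives 0.3675/(0.60 + 0.20) = 45.9%, which is too low.
- With dropout unrelated to stopping, where the present analysis is unbiased, unweighted coding gives 0.343/(0.56 + 0.20) = 45.1%.
- With no true effect (49% and s = 20% in both arms) and unrelated dropout of 25% v 35%, unweighted coding gives 0.3675/0.80 = 45.9% v 0.3185/0.72 = 44.2%, a spurious −1.7 points.

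**The case against.** The strongest reply is that no sentence says a mother with a reported early stop is classed as missing. Table 3 is a collection schedule, and a derivation rule may sit in an analysis plan that is not shown. That is fair as far as it goes. But the article does fix the survey wave, the analysis set and the predictors of the weight model, and followed together these leave the early reports unused. The point is about what is fixed, not about a missing detail.

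A second reply points to the other planned analyses.
- The worst-case analysis counts these mothers as 'no', but it does the same to every mother with an unknown outcome. At s = 20% / 18% and r = 2 it gives 36.7% v 41.8%, against true values of 49% and 56%. It is a bound, not a repair.
- The shared frailty models can use early cessation reports, but they serve duration and not the binary outcome.
- The register-based difference-in-difference study does not depend on survey response, but it waits for data until early 2025 at the earliest. Register linkage is described for the survey analysis too, yet the stated handling of a missing outcome there is weighting, not substitution of the register value.

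A third reply stands in part. The outcome statement reads as current status at four months, while the sample size section speaks of a minimum duration. A reader might infer from the latter and from Definitions that any reported lapse is a final 'no'. The documents do not settle this: a return to exclusive feeding is not addressed, and the stated hypothesis is that supported women overcome difficulties. Only a report that all breastfeeding has stopped is safe to treat as 'no'.

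**Conclusion.** The point holds in a conditional form. As written, the binary analysis discards relevant data that the trial collects, and baseline-only weighting cannot remove a bias driven by early stopping. The excess in the proportion is about 1 to 5 points if stoppers drop out 1.5 to 2 times as often. This rests on assumed early-stopper shares, on baseline variables explaining none of the link, and on stoppers being 'no' at four months.

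A reader might infer more, namely that the primary proportion is certainly overstated and that unequal dropout alone biases the comparison. The documents do not support this. There is no bias if response is unrelated to early stopping given the weighting variables. The arm difference barely moves (7.0 to 7.3 points) when dropout and the link are the same in both arms. It moves to between 3.5 and 10.7 points only in scenarios where the link differs by arm, or where dropout differs while a link exists. Any figure for an inflated type I error would depend on response rates by arm that the documents do not give.

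**What to change.** In the weighted intention-to-treat analysis under Statistical methods:
1. Code as 'no' at four months, with weight 1, any mother who reported at one week or one month that all breastfeeding had stopped, whether or not she answers at four months.
2. Estimate the response weights only among mothers not known to have stopped. Add latest reported feeding status (including a lapse from exclusive feeding) and trial arm to the predictors.
3. Keep the unweighted complete-case analysis as secondary and do not apply the 'no' coding there, since it would bias the proportion downward.

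This recovers the true proportion provided the extended weights explain response among the remaining mothers. The cost is a short change of wording and slightly more analysis work on data already collected. The one downside is that the rare mother who resumes exclusive breastfeeding after reporting full cessation is counted as 'no'.

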#### Eligibility criteria

All women giving birth in the 21 municipalities during the project period from April 2022 to end of 2023 are eligible for inclusion in the trial provided they are: 1) ≥ 15 years old, 2) intend to breastfeed their infant, 3) were discharged from the hospital less than seven days after giving birth^1^, 4) gave birth to a singleton, and 5) had a term born child. The exclusion criteria are: 1) insufficient Danish and English language skills to respond to questionnaires and understand the support conveyed in either Danish or English, 2) known substance use disorder or use of illegal drugs, and/or 3) known morbidity or disablement affecting their ability to breastfeed. Fathers/partners are invited to participate based on their partner’s eligibility and must be able to understand Danish or English.

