### Survey data

The primary outcome measure is studied by using self-reported measures collected via self-administered web-based questionnaires. Survey questionnaires are distributed via emails to mothers recruited via the health visiting programme at the following five postpartum time-points: one week, one month, four months, six months and 12 months. Additionally, fathers/partners were invited to a survey at one month postpartum (see Fig. 3 for an overview timeline). From the surveys, we also study a range of secondary outcome measures.

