### Recruitment to the survey

The health visitors will recruit the families during their first visit after birth. Health visitors have been instructed to inform about the project verbally and in writing in families where the mother meets the eligibility criteria (see information sheet in Appendix A). Enrolment is done by the health visitors who collect families’ consent and help fill in the families’ information in a secure electronic recruitment form. Furthermore, the health visitor assesses whether the mothers qualify for the intensified intervention based on her age and educational level. Participation in the survey and the intensified intervention are independent, i.e., mothers declining participation in the survey may still accept the intensified intervention.

Municipalities will stop recruiting when the required number of mothers with data from the first three questionnaires has been reached, as outlined in the description of the sample size calculation.

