### Data collection

The data collection period commenced on 26 April 2022, in both trial arms. From mid-June it has been possible to assess the full intervention in the intervention clusters, including monitoring the effect achieved by introducing breastfeeding counselling in the pregnancy visit. Local variations will exist in the duration of data collection due to a varying number of births in the clusters. Data collection is projected to end by October 2023 in the municipalities with fewest births.

The questionnaires are distributed to families via personal emails and followed up by two reminders sent by text message (SMS).

Mothers for whom reading and filling out a questionnaire are very challenging are offered a phone call or Microsoft Teams call by a project student assistant who will help them complete the questionnaire. At recruitment, the mother will decide whether to accept or decline this offer.

An overview of the data collection timeline is given in Fig. 3, and Table 3 shows which outcomes and covariates are collected from each survey wave.

**Table 3 Tab3:** Overview of quantitative data collection, source and timepoints

Outcome measures	Survey data						Register data
*Sources*	**Mother**					Partner	
Time point since birth (PP)	One week	One month	Four months	Six months	Twelve months	One month	

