To validate the robustness of the results, the following sensitivity analyses will be performed: First, data will be restricted to mothers having received the full intervention, i.e., including pregnancy visits (June 17 and onwards), to assess the effect of receiving the full intervention compared to mothers having received the intervention without the pregnancy visits (April 26 to June 16); second, observations with no records in registries, most likely an indicator of recent immigration, will be excluded to test whether the effect of the intervention is higher among individuals familiar with the Danish healthcare system than among those who are not familiar with the system; and, third, the worst case scenario assigning no breastfeeding at four months postpartum to all individuals with missing registrations will be used to gauge the minimum effect of the treatment.

The Danish nationwide registries will further allow detailed assessment of selection into the trial (Table 3). Selection into the trial will be examined using register data from 2022, again using inverse probability weighting to assess potential selection effects.

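### The weights for missing four-month outcomes omit trial arm and early breastfeeding status, so they cannot remove dropout that follows early cessation differently in the two arms

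*Protocol article*

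**What the plan says.** **Weights.** Under Statistical methods, missing outcomes in the intention-to-treat analysis are handled by inverse probability weighting. The weights come from "logistic regressions with outcome data (yes vs. no) as dependent variable and the following baseline variables as predictors". The list names maternal education, age, cohabitation and partner's education, and ends with "household income, occupational status, maternal smoking status, maternal BMI, and maternal as well as paternal psychiatric histories". Arm and any measure of breastfeeding after birth are absent.

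**What is available.** Mothers are surveyed "at the following five postpartum time-points: one week, one month, four months, six months and 12 months" (Survey data). In Table 3 the row beginning "Exclusive breastfeeding (continuous" is marked at one week, one month and four months, with the National Child Health Register as a further source.

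**Recruitment.** "The health visitors will recruit the families during their first visit after birth" (Recruitment to the survey). The municipalities were already randomised by then, and the Discussion says allocation cannot be concealed. Mothers must "intend to breastfeed their infant" (Eligibility criteria). In the intensified intervention, offered only in the intervention arm, telephone follow-up stops once a mother stops breastfeeding.

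**Existing safeguards.** There is a worst-case analysis that counts missing as not breastfeeding. There is also a selection check ("Selection into the trial will be examined using register data from 2022") and a register difference-in-difference analysis on all mother–child dyads in the 21 municipalities.

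**The concern.** Weighting removes dropout bias only if, given the variables in the weight model, response no longer depends on the outcome. A mother who has stopped exclusive breastfeeding by one month has in effect settled her four-month outcome. If she is also less likely to answer the four-month questionnaire, early status is the variable the weights most need. If that tendency differs by arm, a single function of baseline variables applied to both arms cannot restore the contrast.

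The outcome model cannot do this job. It adjusts for baseline and design covariates, and early breastfeeding is affected by treatment, so it should not be entered there. The weight model is the proper place for it.

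At stake is whether the intention-to-treat estimate from the survey corrects for informative dropout, or mostly repeats the complete-case result under another name.

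**Working it through.** **1. The plan's own figure.** From Sample size and power calculations: 49% vs 56%, 80% power, 5% significance (taken as two-sided), ICC 0.001, 8 clusters per arm.
- Per arm without clustering: (1.96·√(2·0.525·0.475) + 0.8416·√(0.49·0.51 + 0.56·0.44))² / 0.07² = 798.
- With clustering, 8m = 798·(1 + 0.001(m − 1)), so m = 798·0.999/(8 − 0.798) = 110.7, i.e. 111 as stated. The subgroup (45% vs 55%) gives 392 per arm and m = 51.5, i.e. 52 as stated.

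The arithmetic is sound; the point concerns bias.

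**2. How much is missing.** With 80% participation and 30% attrition, 1 − 0.8·0.7 = 44% of mothers lack the survey outcome. Of this, 20 points are non-participation and 0.8·0.3 = 24 points are attrition after recruitment. Early survey status can help only with the 24.

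**3. Illustration under no effect.** All inputs here are assumptions, not figures from the documents:
- 35% of mothers in the risk group;
- 75% (others) and 62% (risk group) exclusively breastfeeding at one month;
- of those, 72% and 65% still doing so at four months, and none of the rest;
- response 76% and 71% if still breastfeeding at one month, lower by a shortfall if not.

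True rate in both arms: 0.65·0.75·0.72 + 0.35·0.62·0.65 = 49.2%.

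Worked case, shortfall 5 points in control and 20 in intervention:
- Response, others: control 0.75·0.76 + 0.25·0.71 = 0.7475; intervention 0.75·0.76 + 0.25·0.56 = 0.710; pooled 0.7288.
- Response, risk group: control 0.62·0.71 + 0.38·0.66 = 0.691; intervention 0.62·0.71 + 0.38·0.51 = 0.634; pooled 0.6625.
- Four-month rate among responders: control 54.9% and 41.4%; intervention 57.8% and 45.1%.
- Weighting by the inverse of the pooled response in each risk group: control (0.65·0.7475/0.7288·0.549 + 0.35·0.691/0.6625·0.414)/1.032 = 50.1%; intervention, by the same formula, 53.4%.
- False difference: 3.29 points weighted, 3.27 unweighted.

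False difference in points, by what the weights contain:

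| Shortfall control / intervention | None | Baseline only (plan) | + arm | + early status | + status × arm |
|---|---|---|---|---|---|
| 10 / 10 | 0.00 | 0.00 | 0.00 | 0.00 | 0.00 |
| 0 / 10 | 2.05 | 2.06 | 1.99 | 2.12 | 0.00 |
| 5 / 15 | 2.13 | 2.15 | 2.08 | 2.29 | 0.00 |
| 5 / 20 | 3.27 | 3.29 | 3.19 | 3.57 | 0.00 |
| 0 / 20 | 4.27 | 4.30 | 4.16 | 4.58 | 0.00 |
| 5 / 25 | 4.46 | 4.49 | 4.35 | 4.97 | 0.00 |

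The arms are otherwise identical, so swapping the shortfalls reverses the sign. In the 10 / 10 row both rates are overstated (51.2% against 49.2%) but the difference is right. The zeros in the last column follow from letting response depend on nothing beyond arm, risk group and one-month status.

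**4. Arm without early status.** If arm only shifts response overall by 4 points, the bias is 0.03. If arm interacts with risk group (20-point lower response in control, 2-point in intervention), it is −0.85, part of which the covariate-adjusted outcome model would absorb.

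**5. Effect on the test.** At 8 × 111 = 888 per arm and design effect 1 + 110·0.001 = 1.11, SE = √(2·0.25/888·1.11) = 2.5 points. Biases of 2.1, 3.3 and 4.3 points raise the 5% type I error to about 13%, 26% and 40%.

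**6. A true 7-point effect (also assumed, unweighted, no covariates).** One-month rates are 75% and 80%, and response is 77% if still breastfeeding. In control, response is 49% if stopped: 0.75·0.77·0.653/0.70 = 53.9%. Intervention responders: 0.8·0.77·0.70/(0.616 + 0.2·r). The difference is 6.5 points for r = 0.49, 4.7 for r = 0.60 and 8.4 for r = 0.38. The error can go either way.

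**The case against.** **The register analysis already covers all births.** This stands in large part. The difference-in-difference analysis compares the arms on four-month breastfeeding whatever the mother's consent or survey response, so the 44% applies to the survey measure only. It is a separate analysis, expected in early 2025 at the earliest, and leaves the survey weights as they are. The worst-case analysis does not change them either. With unequal missingness it can move the estimate either way, so it is not a guaranteed minimum.

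**The sizes are assumed.** This stands. The documents give no dropout by arm or status. The illustration also uses one binary baseline variable where the plan has ten. A richer list would capture more of early cessation, so the finding that the weights barely move the bias belongs partly to the set-up.

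**Stronger readings that the documents do not support.**
- A reader might infer that adding early status would also repair selective recruitment. It cannot: survey status exists only for recruited mothers.
- A reader might infer that the missing arm term is the main fault. The table shows that arm or status as a main effect leaves the bias in place; their interaction does the work.
- A reader might take "Selection into the trial will be examined using register data from 2022" to exclude 2023, although "Data collection is projected to end by October 2023 in the municipalities with fewest births". The phrase can equally mean from 2022 onwards, which fits the difference-in-difference period. It is an ambiguity to clear up.
- A reader might suppose that counselling at the pregnancy visit moves many mothers across the intention criterion. The Background reports over 97% initiation. A 5% shift with an assumed 15% four-month rate would move an arm by 0.05/1.05·(0.56 − 0.15) = 2.0 points. A 3% shift gives 0.03/1.03·0.41 = 1.2. Initiation is not the same as stated intention, but the larger figure is hard to support.

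**Conclusion.** The point holds for attrition among recruited mothers. The article fixes a predictor list that leaves out arm and early breastfeeding status, both of which the trial will have. This is a choice stated in the article, not a detail left to the analysis plan. Weights built on that list cannot fully remove dropout that depends on early cessation differently by arm. Under the assumed patterns the residual bias is roughly 2 to 4 points (2.1 to 4.5 in the cases run), of either sign, against a 7-point target. It is zero under a null effect when cessation-related dropout is equal across arms.

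Differential dropout is plausible given open allocation and contact that ends at cessation in one arm only, but it is not shown. The documents do not support the wider claims that the same change would correct recruitment, that the selection check omits 2023, or that recruitment selection goes unchecked.

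**What to change.** 1. **Attrition, among recruited mothers.** Fit the weights separately by arm, or with arm-by-status interactions. Keep the listed predictors and add exclusive breastfeeding at one week and one month. Where the one-month wave is missing, use sequential weights or imputation.
2. **Recruitment, as a separate step.** Fit an arm-specific participation model on covariates available in the registers for all births. Table 3 shows no register source for smoking or BMI, so either leave them out of this model or say how they will be obtained.
3. **Selection check.** State that it covers the whole recruitment period in each municipality, including 2023.
4. **Cross-reference.** Name the planned register analysis of all births as the check on recruitment selection.

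The cost is a change of wording in the analysis plan and modest extra modelling on data already collected or due to be linked. The weights will be somewhat more variable, and the register check arrives only when the register data do.
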